**Methods:**

This observational study will recruit six- to eight-month old infants with moderate to severe AD and age-matched control infants who do not have AD. At six-eight months diurnal sleep electroencephalography and polysomnography will be performed in our research center. Nocturnal sleep actigraphy will be performed at home for five consecutive nights at six-eight months and 12 months. Between six and 12 months, monthly questionnaires will capture data on quantitative sleep and parental sleep. Skin barrier and immune profiles will be captured at six-eight and 12 months. AD will be assessed using standardized severity assessment tools and treated according to protocol. A neurodevelopmental assessment will be performed at 18 months to assess cognition and behaviour. An estimated sample size of 50 participants in each group is required to power the primary outcome of disturbed macrostructure of sleep and secondary outcomes of disturbed microstructure of sleep, and disturbed parental sleep, assuming an attrition rate of 60%. Potential confounding factors which will be controlled for in the data analysis will include parental educational level, parental depression, feeding practice, and number of siblings.

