To calculate the sample size, an incidence of sleep disturbance of 60% in the infants with moderate to severe AD [17] and an incidence of 25% in healthy controls [54] will be assumed. Therefore, aiming for a power of 80% and a significance level of 5%, a total sample size of 30 subjects will be required for each group to power the dichotomous primary outcome of disturbed macrostructure of sleep and secondary outcome of disturbed microstructure of sleep. Assuming a worst-case attrition rate of 60%, and to ensure that data are available at all time points, 50 subjects will be required for each group, with a total number of participants of 100.

For descriptive statistics, mean ± standard deviation will be used, median and interquartile range for quantitative variables, and percentage with number for categories. Spearman (parametric) or Pearson (non-parametric) correlations will be applied to determine the association between dependent and independent (parental and infantile) variables. Independent variables will be fitted to logistic and linear regression models to evaluate interactions as well as to identify confounding factors. All the analyses will be carried out with the statistical software Stata, considering a *p* < 0.05 as cut-off for statistical significance. For sleep diaries, mean questionnaire scores and subsections will be compared between groups. For actigraphy, total number of overnight movements will be compared between groups. For EEG, the number, power, and density of sleep spindles, and sleep staging will be compared between groups. For parental sleep, mean questionnaire scores will be compared between groups, and qualitative parental interviews will be performed with a selection of parents of infants with AD. Qualitative data will be processed using NVIVO software.

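### The sample size of 50 per group does not fit the stated 60% attrition: 20 per group would remain, not the 30 required; 50 fits 40% attrition

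*Protocol article*

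**What the plan says.** The sample-size paragraph in Methods/design assumes "an incidence of sleep disturbance of 60% in the infants with moderate to severe AD" and "an incidence of 25% in healthy controls", with 80% power and 5% significance. From this, "a total sample size of 30 subjects will be required for each group to power the dichotomous primary outcome of disturbed macrostructure of sleep"; the same number is applied to the microstructure outcome. The next sentence allows for loss to follow-up: "Assuming a worst-case attrition rate of 60%, and to ensure that data are available at all time points, 50 subjects will be required" in each group, 100 in total.

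The Methods paragraph of the Abstract repeats the pairing. It gives 50 per group as the number that powers the primary and secondary outcomes, "assuming an attrition rate of 60"%.

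Methods/design places the primary outcome (sleep efficiency and night-time awakenings) at 12 months. Enrolment is at six to eight months, the sleep EEG is recorded at the first visit, and the last visit is at 18 months.

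**The concern.** An allowance for attrition should leave the required number of evaluable participants after the stated loss. Here it does not: a 60% loss from 50 falls short of 30. Either the attrition rate or the enrolment figure is wrong.

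What is at stake is the power claimed for the primary outcome. It is measured four to six months after enrolment, so loss to follow-up bears on it directly. The paragraph presents 50 per group as enough under a stated worst case, and as written that assurance fails. Someone planning recruitment, or later judging a null 12-month result, could not tell from the article which loss the design was built to absorb.

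**Working it through.** **Inputs** (sample-size paragraph, Methods/design): p1 = 0.60, p2 = 0.25, α = 0.05, power 80%, 30 evaluable per group, attrition 60%, 50 enrolled per group. Sidedness is not stated; two-sided is assumed, with one-sided shown as a check.

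**Step 1. Reproduce the 30.** With p̄ = 0.425, the pooled formula is

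n = [z(0.975)·√(2p̄(1−p̄)) + z(0.80)·√(p1(1−p1) + p2(1−p2))]² / (p1−p2)²

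= [1.960 × 0.6991 + 0.8416 × 0.6538]² / 0.35² = 1.9205² / 0.1225 = 30.1 per group.

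The arcsine formula gives 29.9. The plan's 30 is therefore sound, apart from rounding.

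**Step 2. Apply the attrition.**

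- Remaining from 50 at 60% loss: 50 × (1 − 0.60) = 20.
- Needed to keep 30 at 60% loss: 30 / (1 − 0.60) = 75 per group, 150 in total.
- Loss at which 50 leaves 30: 1 − 30/50 = 40%.

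Two routes could have led to 50. One is 30/0.60 = 50 exactly, which treats 60% as retention. The other is 30 × 1.60 = 48, rounded up. The article does not say which was used, and neither makes 50 enrolled yield 30 at 60% attrition.

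**Step 3. Power at what remains.** With the same pooled approximation,

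power = Φ{[(p1−p2)√n − z(0.975)·√(2p̄(1−p̄))] / √(p1(1−p1) + p2(1−p2))}.

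- n = 30: (0.35 × 5.477 − 1.370) / 0.6538 = 0.836, so power is 79.9%.
- n = 20: (0.35 × 4.472 − 1.370) / 0.6538 = 0.298, so power is 61.7%.

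**Step 4. Does the shortfall depend on the method?**

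| Method | 30 per group | 20 per group |
|---|---|---|
| Pooled normal, two-sided | 79.9% | 61.7% |
| Arcsine, two-sided | 80.2% | 63.0% |
| Unpooled normal, two-sided | 83.4% | 66.8% |
| Uncorrected chi-square, exact power | 80.2% | 61.0% |
| Fisher's exact test | 71.9% | 49.3% |
| Pooled normal, one-sided | 88.0% | 73.7% |

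At 20 per group every method falls below 80%.

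**Step 5. Loss by 12 months below 60%.** The pooled formula, with 50 enrolled per group, gives:

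| Loss by 12 months | Left per group | Power |
|---|---|---|
| 20% | 40 | 90% |
| 40% | 30 | 80% |
| 50% | 25 | 72% |
| 60% | 20 | 62% |

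**The case against.** The strongest reply is that 40% attrition was meant. Then 50 per group is right, 30 remain, power is about 80%, and the only defect is a misworded rate. This stands as a plausible reading, helped by 30/0.60 giving exactly 50. It does not remove the contradiction, because the article says 60% attrition in two places and nothing elsewhere corrects it.

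The second reply is that 60% is labelled a worst case and is tied to having data at all time points, with follow-up to 18 months. Loss by the 12-month outcome could be smaller, and the Discussion describes design choices meant to support retention. This also stands and limits the power figure: 62% applies only if 60% are lost in both groups by 12 months. But the allowance is offered as covering the worst case, and that is where it fails.

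Third, the shortfall does not reach every outcome. The EEG is recorded at the first visit, so dropout after enrolment hardly touches the microstructure comparison.

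A reader might infer more than the article supports:

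- **That the study simply has 62% power.** It does not follow; the figure depends on the stated loss occurring.
- **That the authors certainly divided by 0.60.** The article does not show the calculation, and 48 rounded up is also possible.
- **That analysing sleep efficiency as a continuous measure would restore the power.** The article gives no mean, standard deviation or cut-off for sleep efficiency. The 60% and 25% are incidences of sleep disturbance, and the switch would leave out night-time awakenings, which belong to the primary outcome.

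**Conclusion.** Wrong as written. The requirement of 30 per group is reproducible, but 50 enrolled with 60% attrition leaves 20. The stated attrition and the stated sample size cannot both stand, in the Abstract or in Methods/design. Either the rate should be 40%, in which case the design is as intended, or the rate is 60% and the enrolment is 25 per group short of the 75 needed.

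On the second reading, power for the dichotomous 12-month outcome in the stated worst case is about 62%. The chance of missing the assumed difference is then about 38%, against the planned 20%. This rests on the article's own 60% v 25%, a two-sided 5% test by normal approximation, and equal loss of 60% in both groups by 12 months. One-sided, power would be about 74%. The documents do not show which reading was intended.

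**What to change.** Correct the Abstract and the sample-size paragraph together so that attrition, enrolment and power agree. Two corrections need no change in recruitment:

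1. If 50 was built on 60% retention, restate the allowance as attrition of up to 40% (60% retention). The 30 evaluable, 50 enrolled and 80% power then agree.
2. If 60% attrition is really the worst case, keep it and state that 20 per group would remain, with about 62% power for the dichotomous 12-month outcome (two-sided normal approximation).

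Under the second, add that 80% power at 60% attrition would need 75 per group (150 in total). Whether recruitment could change is for the investigators; the article gives no basis for judging it. Under either correction, say that the allowance concerns outcomes measured after enrolment and not the first-visit EEG.

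The cost is a wording change in two places. The first option changes the stated rate only. The second replaces a favourable power figure with a less favourable one. Neither needs extra infants.

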### Study objectives

The research question of this study is: do infants with early-onset AD have disrupted quantity and quality of sleep in the first year of life, compared to healthy controls, and does the degree of sleep disruption correlate with the severity of AD? Our hypothesis is that infants with early-onset AD have impaired quantity and quality of sleep in the first year of life, which correlates with the severity of AD.

The aim of the project is to describe, for the first time, detailed sleep architecture of infants with early-onset atopic dermatitis (AD), compared to controls, by using EEG polysomnography, sleep actigraphy, and parental reporting.

The objectives are to:Recruit a cohort of infants with early-onset AD and a cohort of matched healthy controlsCollect and analyze parent-reported, actigraphy, and EEG polysomnography sleep data from infants with early-onset AD, and compare to healthy controlsPerform serial clinical assessment, skin barrier assessment, and inflammatory cytokine assessment (by tape stripping), and correlate with sleep features in infants with early-onset ADExamine sleep and quality of life indices of caregivers of infants with early-onset AD compared to controls

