At the first visit at six-eight months of age, infants will be assessed in the INFANT Research Centre in CUH for suitability for entry to the study. The study will be discussed with the parent(s)/guardian(s). If written consent is provided, a baseline assessment will be made. Anthropometric assessment will involve measurement of weight, length, and head circumference. All parents will be asked to complete detailed questionnaires about demographics, environmental factors (home location, ambient bedroom noise, number of siblings), parental educational attainment, feeding practices, and family history of atopic disease. The Maternal Post Natal Attachment Scale and The Edinburgh Post Natal Depression Scale will also be completed at this visit. These questionnaires will collect data about potential confounding factors. Parents will be asked about specific sleep problems with a thorough history of the infant’s 24-hour routine, focusing on naps and sleep routine, sleep environment (crib or parent’s room), sleep position (prone or supine), and need for sleep aids (eg soother, rocking, patting). Parents will be asked to complete the Pittsburgh Sleep Quality Index, a self-report questionnaire that assesses sleep quality over a one-month time interval [43].

For cases, AD will be diagnosed using the Hanifin and Rajka criteria [44]. Severity will be assessed by the Investigator Global Assessment (IGA), Eczema Area and Severity (EASI), and Scoring Atopic Dermatitis (SCORAD) scores [45, 46]. Moderate AD will be defined as IGA 3, EASI 7-12, or SCORAD 15-40. Severe AD will be defined as IGA 4, EASI > 12, or SCORAD > 40. Symptoms and quality of life will be assessed using the Patient-Orientated Eczema measure, Pruritus Numerical Rating Scale with a visual analogue scale, and Infants’ Dermatitis Quality of Life Index [47–49]. The influence of AD on parental quality of life will be assessed using the Dermatitis Family Impact Questionnaire [50]. Previous treatments for AD will be documented.

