At 18 months, subjects will be brought back to the INFANT Research Centre for their final study visit. At this visit weight, height, and head circumference will be measured. Mothers will be asked to fill out the Beck Depression Inventory. For cases, AD status and severity will be reassessed. In addition, a neurodevelopmental screening protocol will be completed to screen for behavioural difficulties and to ensure that all the participants are normally developing. This assessment will be performed using the CogniTOT touchscreen app (Liltoda, Cork, Ireland). CogniTOT is a touchscreen-based 10- to 15-minute cognitive assessment designed to screen for cognitive delay in young children aged 18-30 months with good concurrent validity with the Bayley’s Scales of Infant Development [53]. It will be suitable to use even if current social restrictions continue. Behaviour will be assessed using parental questionnaires. The Achenbach Child Behaviour Checklist 1 ½ - 5 is a widely-used questionnaire to assess behavioural and emotional difficulties, filled out by parents. It assesses internalizing (i.e., anxious, depressive, and over-controlled) and externalizing (i.e., aggressive, hyperactive, noncompliant, and under-controlled) behaviours. Several sub-areas are also measured, including anxiety and depression, and ‘Sleep Problems syndrome’. The Modified Checklist for Autism in Toddlers, Revised is a screening questionnaire for autism spectrum disorder. Any worrying or incidental findings will be referred for follow up along the relevant clinical pathway.

The primary outcome will be altered macrostructure of sleep at 12 months (sleep diary and actigraphy), measured as decreased sleep efficiency and increased night time awakenings. The secondary outcomes will be altered microstructure of sleep at six-eight months, measured as sleep spindle power and power in REM and NREM sleep stages; and parental sleep quality and quality of life. Outcomes will be correlated with severity of AD and inflammatory cytokines at six-eight and 12 months. In terms of safety outcomes, the clinical, neurophysiological and cytokine analyses are all safe and well-tolerated procedures with no significant associated risks. Potential confounding factors which will be controlled for in the data analysis will include parental educational level, parental depression, feeding practice, and number of siblings.

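### The correlation rule has its labels reversed: Spearman is called parametric and Pearson non-parametric

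*Protocol article*

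**What the plan says.** The rule for correlation stands in the statistical paragraph of Methods/design in the protocol article: "Spearman (parametric) or Pearson (non-parametric) correlations will be applied to determine the association between dependent and independent" variables. The two bracketed labels are the only guidance on when each coefficient applies; no normality check or other criterion is stated. The same paragraph sets p < "0.05 as cut-off for statistical significance".

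Three other places show where the rule is used or what it is used on:

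- Study objectives asks whether infants with AD have disrupted sleep and then "does the degree of sleep disruption correlate with the severity of AD". The hypothesis repeats this second limb.
- The outcomes paragraph of Methods/design says "Outcomes will be correlated with severity of AD and inflammatory cytokines at six-eight and 12 months".
- The description of the first visit says "Severity will be assessed by the Investigator Global Assessment (IGA), Eczema Area and Severity (EASI), and Scoring Atopic Dermatitis (SCORAD) scores". IGA is a graded, ordinal scale.

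No other sentence in the article restates or corrects the labels.

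**The concern.** Pearson's coefficient measures linear association, and its usual test rests on normal theory. Spearman's coefficient works on ranks and needs no distributional form. The plan attaches each label to the wrong method, so both branches of the rule are wrong when read as written: variables judged unsuitable for a parametric method are sent to Pearson, and normal variables to Spearman.

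At stake are the correlations of sleep with AD severity and with skin cytokines. These answer the second limb of the research question. Pearson on strongly skewed data depends heavily on a few large values, so a real association can be underestimated or missed. The opposite mistake, Spearman on normal data, costs much less. A reader also cannot tell whether the method names or the labels carry the intent, so either coefficient could later be defended as the planned one.

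**Working it through.** **Step 1: the labels, by definition.** No arithmetic is needed.

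- Pearson: r = Σ(xᵢ − x̄)(yᵢ − ȳ) / √[Σ(xᵢ − x̄)² · Σ(yᵢ − ȳ)²], computed on the measured values. This is the parametric coefficient.
- Spearman: the same formula applied to the ranks of x and y. This is the non-parametric coefficient.

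The article has these reversed.

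**Step 2: what the sentence governs.** The severity and cytokine correlations in Study objectives and in the outcomes paragraph fall under it. The sample size does not. That rests on two proportions, "an incidence of sleep disturbance of 60% in the infants with moderate to severe AD" and "an incidence of 25% in healthy controls", and no correlation enters it. As a check on the plan's own figure, the two-sided, uncorrected formula for 60% against 25%, at 80% power and 5% significance, gives 31 per group. Power at the stated 30 is 79.9%. The stated size therefore reproduces to within one infant, and it is the same whichever coefficient is used later.

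**Step 3: how large the effect could be.** The inputs are:

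- n = 30, the stated evaluable number per group. The AD group is the relevant one, because severity is a measure of the disease.
- Two-sided 5% level, from the plan.
- Underlying correlation 0.5: an assumption, not in the documents.
- Skew: log-normal with log-SD 1.0 or 1.5, also an assumption. The documents give no distribution for cytokines or severity scores.

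Draw x and e as independent standard normals and set y = 0.5x + √(1 − 0.5²)·e. For one skewed variable, replace x by exp(σx). For two, replace y by exp(σy) as well. Test each dataset with both coefficients. Spearman is unchanged by the exponential, because ranks are unchanged.

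| Setting, n = 30 | Pearson power | Spearman power |
|---|---|---|
| Both normal | 82-83% | 77% |
| One log-normal, log-SD 1.0 | 68% | 77% |
| One log-normal, log-SD 1.5 | 55-56% | 77% |
| Both log-normal, log-SD 1.0 | 58% | 77% |
| Both log-normal, log-SD 1.5 | 46-47% | 77-78% |

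Ranges reflect repeated runs. The reversed rule uses the Spearman column in the first row and the Pearson column in the others. The loss is therefore 82 − 77 = 5 to 83 − 77 = 6 points with normal data, and 77 − 68 = 9 to 77 − 55 = 22 points with one skewed variable.

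The mean coefficient with one skewed variable is 0.42 (log-SD 1.0) or 0.37-0.38 (log-SD 1.5) for Pearson, against 0.47 for Spearman. Closed forms point the same way. The population Pearson value is 0.5σ/√(exp(σ²) − 1), which is 0.5/√1.718 = 0.38 at σ = 1.0 and 0.75/√8.488 = 0.26 at σ = 1.5. The Spearman value is (6/π)·arcsin(0.25) = 0.48 at any σ. Sample means of Pearson lie above its population value here, because small samples often miss the extreme values that lower it.

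**Step 4: other sample sizes and false positives.** With both variables log-normal, power is 39-46% (Pearson) against 57-58% (Spearman) at n = 20, and 57-76% against 94-95% at n = 50. With no true correlation, and n from 20 to 50, the rejection rate is 5.0-6.4% for Pearson and 4.6-5.5% for Spearman.

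**The case against.** The strongest reply is that this is a transposition in one sentence. An analyst who knows both methods would use them correctly whatever the brackets say. That may well be so, but intent cannot be established from the article, and the sentence is the only selection rule it gives.

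A reader might infer more than the text supports, in four ways:

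- *That skewed cytokine and severity data will get the wrong test.* The article never says these data are skewed. The consequence follows only if a variable is judged non-normal or ordinal and the labels are then followed literally. The most that can be said is that it could happen. IGA is the clearest case, because its ordinal nature needs no assumption about skew.
- *That the percentages describe this trial.* They do not. Both the correlation of 0.5 and the log-SDs are assumed. The simulation contains no ordinal, bounded or count variable, and more than 30 cases may be available at the first visit. A loss remains at n = 50 under the same assumptions, but its true size here is unknown.
- *That false findings become more likely.* Type I error stays close to 5% with either coefficient.
- *That the main conclusion is at risk.* The primary outcome is a comparison between groups, which this sentence does not govern. The plan also provides logistic and linear regression, so the coefficient is not the only analysis of these associations.

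It might also be asked that the coefficient be fixed variable by variable. An article may leave that to the analysis plan, which is not shown, so its absence is no finding. All these limits stand. None of them makes the labels right.

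**Conclusion.** The sentence is wrong as written, and that conclusion needs no assumption. It is an operative analysis rule and should be corrected, but the consequence is modest and confined to the correlation analyses.

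If the rule is followed literally and a variable is non-normal, the cost is reduced power and a smaller coefficient. The size is about 55-68% power instead of 77%, given 30 infants, an assumed underlying correlation of 0.5 and assumed log-normal skew in one variable. For normal variables the cost is about 5-6 points. The documents support neither a claim that the error will occur in practice nor one that it reaches the sample size or the primary comparison.

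**What to change.** Exchange the two names, so that the sentence reads: *Pearson (parametric) or Spearman (non-parametric) correlations*. If a separate analysis plan carries the same sentence, correct it there too. The change is one sentence. It alters no stated figure, no data collection and no sample size, and it has no operational cost.

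### If the dichotomous primary outcome goes into standard logistic regression with four confounders and interactions, about 17 to 26 expected events are too few, and at the planning effect the AD odds ratio is biased upward by about 20% to 35%

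*Protocol article*

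**What the plan says.** All the relevant text is in Methods/design of the protocol article.

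- Sample size: the planning rates are "an incidence of sleep disturbance of 60% in the infants with moderate to severe AD" and "an incidence of 25% in healthy controls". From these, "a total sample size of 30 subjects will be required for each group to power the dichotomous primary outcome". Fifty per group are to be recruited, with a worst-case attrition of 60%.
- Outcomes: the primary outcome is sleep macrostructure at 12 months, taken from diary and actigraphy as sleep efficiency and night awakenings. The confounders to be "controlled for in the data analysis will include parental educational level, parental depression, feeding practice, and number of siblings".
- Analysis: "Independent variables will be fitted to logistic and linear regression models to evaluate interactions as well as to identify confounding factors". The paragraph does not say which model serves which outcome, how the model is estimated, how the confounders are coded or which interactions are meant. It also plans to compare mean diary scores and total overnight movements between groups.

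**The concern.** A dichotomous outcome, a commitment to adjust for four factors and the naming of logistic regression together point to a logistic model for the outcome on which the study is sized. At these numbers, maximum-likelihood logistic regression has a known weakness. When there are few events per coefficient, the estimated odds ratio is biased away from 1, and some fits have no finite solution because of separation. Fixing the covariate list in advance does not remove this.

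The adjusted effect of AD on infant sleep would then be overstated if the true effect is near the one planned for. Part of the gap between the adjusted and unadjusted odds ratios could also be mistaken for confounding.

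**Working it through.** **Inputs from the article.** Rates 0.60 and 0.25; power 80%; significance level 5% (two-sided assumed); 30 evaluable per group; 50 recruited per group; worst-case attrition 60%; four named confounders.

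**The plan's own figure.** With the pooled two-proportion formula,

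n = [1.96 × √(2 × 0.425 × 0.575) + 0.842 × √(0.60 × 0.40 + 0.25 × 0.75)]² / 0.35² ≈ 30.1,

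which rounds up to 31. Power at 30 per group is 79.9%, so the stated 30 reproduces.

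**Numbers available.** The sized case is 30 per group. Taking the attrition figure at face value, 50 × (1 − 0.60) = 20 per group. The step from 30 to 50 fits 60% retention (30 / 0.60 = 50) and not 60% attrition (30 / 0.40 = 75). That is a separate inconsistency, and the 20-per-group case depends on it.

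**Planning effect as an odds ratio.** (0.60 / 0.40) / (0.25 / 0.75) = 4.5.

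**Events per coefficient.** Expected events are n × (0.60 + 0.25), which is the smaller outcome class.
- 30 per group: 25.5 events. Group plus four single-term confounders: 25.5 / 5 = 5.1. With four AD-by-covariate interactions: 25.5 / 9 = 2.8.
- 20 per group: 17 events. 17 / 5 = 3.4, and 17 / 9 = 1.9.
- 50 per group (no loss): 42.5 events. 42.5 / 5 = 8.5, and 42.5 / 9 = 4.7.

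**Simulation of the main-effects model.** Maximum likelihood, 3,000 trials per setting, control rate 25%. The article gives no covariate effects, so these are assumptions: four one-term covariates (two binary, two continuous), modest effects (log odds of 0.3 each in the runs across true odds ratios), either balanced between groups or shifted. Fits that separated or failed were left out. Inflation is estimated over true odds ratio.

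| Per group | Median, true OR 4.5 | Mean on log scale, true OR 4.5 | Mean on log scale, true OR 2 | Mean on log scale, true OR 1 |
|---|---|---|---|---|
| 20 | 30-33% | 44-53% | 16-18% | none (within 3%) |
| 30 | 18-22% | 22-27% | 9% | none (within 1%) |
| 50 | 9-12% | 11-14% | 5-6% | none (within 1%) |

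Two further simulations at true odds ratio 4.5 gave medians of 5.2 and 5.5 at 30 per group (5.2 / 4.5 = 1.16; 5.5 / 4.5 = 1.22), and 5.7 and 6.1 at 20 per group (1.27 and 1.36). In round figures the median bias is about 20% and 30-35%.

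**Richer models.** With four AD-by-covariate interactions at true odds ratio 4.5, about 8% of fits separated or failed at 30 per group and 32-37% at 20. Among the fits that existed, mean log-scale inflation was 45-56% and 51-64%. If the four confounders took seven degrees of freedom in all (an assumption about coding), it was 42-46% at 30 per group and 86-97% at 20.

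**Firth penalty, same main-effects model.** Inflation falls to 1% at 30 per group and 0% at 20. With the four interactions it is 6% at both.

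**The case against.** **The model is not assigned.** The article never says that the primary outcome goes into a logistic model. Sleep efficiency and awakenings could be analysed by linear models, and the comparisons that are spelled out use means and counts, where this bias does not arise. Estimator, coding and the interaction list can also be left to a fuller document. This stands, and it is why the point is conditional. It does not dispose of the point, because the article itself fixes the sample size, the dichotomous sizing, the four confounders and the evaluation of interactions.

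**The size depends on the effect and on retention.** A reader might infer that the odds ratio is always inflated by 20-55%. The figures do not support that. Such a range describes the log-scale mean, near the planning effect, with 40 to 60 infants. The bias vanishes at an odds ratio of 1, and at 4.5 it is about 11-14% on that scale if all 100 infants are retained. Even with no covariates it is 10% at 40 infants and 7% at 60, so the confounders cause only part of it.

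**False positives.** A reader might infer that the 5% level is badly exceeded. In main-effects simulations under no effect, Wald tests rejected 3.8-6.0%. Likelihood-ratio tests rejected 5.9-8.8%, highest at 20 per group, but the article names no such test. Wald coverage at odds ratio 4.5 was 93-99%. No material harm is shown.

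**Scale.** A reader might infer that sizing on two proportions makes an odds ratio the wrong summary. It does not; sizing that way commits the study to neither scale. The covariate-standardised risk difference from the unpenalised main-effects fit is also nearly unbiased (0.333 against a true 0.327 at 30 per group), while uncorrected Firth probabilities make it about 6-12% too small at 20 to 30 per group. This stands, and it limits what Firth should be used for.

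**Conclusion.** The point holds in conditional form. If the dichotomous primary outcome is analysed by standard logistic regression, group plus four confounders rests on about 3.4 to 5.1 expected events per coefficient. At the planning odds ratio of 4.5, the median estimate is then too high by about 20% at 30 per group and 30-35% at 20. Interactions make this worse, and a sizeable share of fits may not exist.

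This assumes single-term confounders with modest effects, unpenalised fitting and, for the larger figure, that the stated 60% attrition is meant literally. It is a worthwhile, inexpensive improvement to the estimate of effect. It is not evidence that the group comparison is invalid.

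**What to change.** For any dichotomous outcome:
- Estimate the adjusted odds ratio by Firth penalised logistic regression, with profile-penalised-likelihood intervals.
- Enter each of the four confounders as a single term.
- Keep interactions in exploratory models, outside the primary one. This preserves the article's stated wish to look at them.
- If a covariate-standardised risk difference is also reported, take it from the unpenalised main-effects fit or from an intercept-corrected Firth fit, not from uncorrected Firth probabilities.

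The cost is a change of analysis wording; recruitment and data collection are untouched. The downside is a slightly less impressive odds ratio and slightly fewer nominal rejections.
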